### Recruitment

The recruitment of GPs for study participation takes place three months prior to the start of the intervention phase by the three participating regional Associations of Statutory Health Insurance Physicians (ASHIP) Schleswig-Holstein, North Rhine and Westphalia-Lippe, considering the available contingent of participants in their region. In Germany, the ASHIP are bodies under public law, which represent all physicians and psychotherapists treating compulsory insured patients. First, all potentially eligible GPs in the three regions, meaning GPs participating in primary care according to § 73 (1a) SGB V (excluding paediatricians), who have vaccinated patients aged 60 and older insured by the substitute health insurance fund in the past, will be identified. Substitute health insurance funds are a type of health insurance fund with the largest percentage of insured persons on the German market. There are no other major differences between this and other types of health insurance funds. Subsequently, these GPs will be stratified by the three ASHIPs, and randomised into two groups (intervention/control). The potential participating GPs in the intervention group will be contacted by the responsible ASHIP and receive the offer to participate in the intervention group. It is pointed out that participation in the intervention is also associated with participation in the accompanying evaluation study. Subsequently, all enrolled GPs, as well as at least one medical assistant from the practice, complete the online training that is completed after an online knowledge test and submit the certificate of successful participation to the associated ASHIP.

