
### Description of the complex intervention

Against the aforementioned background, a bundle of measures to increase vaccination uptake will be implemented in GP practices. The aim of the intervention is to raise further awareness among GPs and medical assistants about the importance of vaccinations for patients aged 60 and older, to provide them with training in vaccination expertise and communication psychology, to introduce suitable tools for vaccination recall into their practice routines, and to update them on where to find target group appropriate information for patients.

As the first component of the intervention, GPs and their medical assistants complete an accredited online training. The main goal of the online training is to increase medical knowledge about vaccinations and vaccination counselling skills. This is intended to promote vaccine-related communication between GPs and patients, improve patient vaccine literacy, and thereby increase vaccination uptake. Furthermore, participating GP practices will receive a first material package containing appointment reminder cards, a poster on vaccination, checklists on the vaccination procedure in outpatient care and nursing homes, an infosheet with the most important contents from the online training, an immunisation schedule with an overview of recommended vaccinations, and templates of consent forms for vaccination reminders for the following influenza vaccination season.

In the second year of the intervention, the GP practices will again receive a second material package before the start of the influenza vaccination period. This contains, among other things, the materials needed for the upcoming vaccination recall (customisable postcards and matching envelopes). The intervention is planned to be implemented in the GP practices from 01.07.2022 to 31.03.2024. Figure 1 shows the components of the complex intervention.

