Thus, it is assumed in the following that the influenza vaccination uptake rate as primary outcome increases by 3% as a result of the intervention. This 3%-increase should be seen as an initial change. To detect this effect in the secondary data analysis with a power of 90% at a significance level of alpha = 5% (two-sided), 17,508 patients would be needed without considering the cluster effect. Based on available anonymised data from previous studies [32, 33], the intra-cluster correlation (ICC) is expected to be 0.08. With a mean cluster size of 48 patients per practice vaccinated against influenza on average, this results in a design effect of 4.76 and a corresponding required case number of 83,338 patients. Accordingly, about 1736 GPs would be needed (868 GPs in the intervention and control groups each). Likewise, an increase of 3% is also targeted for increase in vaccination uptake rate of further recommended vaccinations as the secondary outcomes. Since the assumed cluster size is reduced to 28, resulting in a design effect of 3.16 with an ICC of 0.08, a case number of 55,325 patients is required for these analyses. For this, 1976 GPs are needed according to the cluster size – 988 GPs in each of the intervention and control groups. Therefore, due to the smaller cluster size for the secondary outcome, a total of 988 GPs is required for the intervention group for the analysis. To ensure that the required number of cases will be achieved, an additional 7% (69 GPs) was added to the calculated number of cases. This resulted in a required total number of 1057 GPs per group.

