##### Qualitative interviews with patients, GPs, and medical assistants

For the individual interviews, GPs and medical assistants in the participating GP practices will be recruited by telephone by the research team using purposeful sampling [37] (by gender, age, region, and individual vs. joint practice). GPs and medical assistants will be recruited preferably from the 50 intervention practices participating in the patient survey to enable integrated analyses of quantitative and qualitative data from the same practices. The recruited GPs and medical assistants will receive information on the study and consent forms in advance. The interviews can take place in the GP practice, at a location of their choice, or by telephone and will be audio-recorded. For the interview, which will last up to 60 min, a financial incentive is planned (50 € per interview).

For the patient interviews, participants will be recruited via the participating intervention practices (n = 50) using purposeful sampling (by gender, age, and region). The intervention GP practices will approach potential interview participants and will invite them to participate in the interview study. The research team will contact the patients and will arrange an interview appointment. The interviews will be conducted by the research team in the patients’ homes, at a location of their choice, or by telephone, and will be audio-recorded.

The estimated number of interviews in the three groups aligns with the recommendation of 20 to 30 interviews per interviewed group suggested by Flick et al. [38]. Accordingly, 30 interviews with patients, 20 interviews with GPs, and 20 interviews with medical assistants are planned. The higher number of interviews with patients is due to the fact that a higher heterogeneity, e.g., in terms of socio-demographic characteristics is expected. Flick [39] advocates the number of cases mentioned in order to obtain manageable and useful data.

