### Measures

#### Secondary data collection

The influenza vaccination rate as primary outcome is measured annually for patients insured by a substitute health insurance fund aged 60 and older. The rate will be computed as the fraction of the amount of vaccinated patients insured by a substitute health insurance fund aged 60 and older and all patients insured by a substitute health insurance fund aged 60 and older of the practice under consideration.

The determination of the secondary outcome, vaccination uptake rates for vaccinations recommended by the STIKO for patients aged 60 and older (except for influenza), is more challenging. This is due to the unclear size of the basic population, which, in turn, is a result of the long periods of time between recommended booster vaccinations (the boosters for tetanus, diphtheria, and pertussis are needed/recommended only every 10 years).

If a sufficiently high number of cases is reached, subgroup analyses for different vaccinations are planned (e.g., for pneumococci and herpes zoster).

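### GPs are randomised individually, but the intervention and the primary outcome rate belong to the practice, so joint practices can fall into both arms and dilute the contrast

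*Protocol article*

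**What the plan says.** **Allocation.** The Recruitment section starts from GPs: "First, all potentially eligible GPs in the three regions, meaning GPs participating in primary care". It then states that "these GPs will be stratified by the three ASHIPs, and randomised into two groups (intervention/control". Under the secondary-data part of the same section, participation is flagged in the billing data for the individual GP.

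**Intervention.** The description of the complex intervention works at practice level: "a bundle of measures to increase vaccination uptake will be implemented in GP practices". It adds that "participating GP practices will receive a first material package containing appointment reminder cards, a poster on vaccination", and one aim is "to introduce suitable tools for vaccination recall into their practice routines". Recruitment also requires at least one medical assistant of the practice to complete the training.

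**Primary outcome.** Under Secondary data collection, the denominator of the influenza vaccination rate is "all patients insured by a substitute health insurance fund aged 60 and older of the practice under consideration".

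**Joint practices.** Interviewees are to be sampled "by gender, age, region, and individual vs. joint practice", so practices with more than one GP are among the participants.

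**Sample size.** The Sample section takes a mean of 48 patients per practice and an ICC of 0.08, and concludes that "about 1736 GPs would be needed (868 GPs in the intervention and control groups each". The final target is 1057 GPs per group.

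**The concern.** Three units that should coincide do not: the GP is allocated, the practice is treated, and the practice is measured. Nothing in the article restricts the trial to single-GP practices, admits one GP per practice, or assigns all GPs of a practice together.

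Two things follow if the text is carried out as written:

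- A joint practice can have one GP in each arm. Under the stated outcome definition it has one rate, which would count on both sides. The control GP also works with the trained assistant, the poster and the recall system once the partner takes part. Both effects bias the comparison towards no difference.
- Several GPs of one practice can fall into the same arm. They share patients, staff and one rate, so they are not independent clusters. The sample-size step from patients per practice to a number of GPs counts them as if they were.

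At stake are a diluted effect estimate, lower power than planned and, if the GP is used as the cluster, standard errors that are too small.

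**Working it through.** **1. The plan's own chain.** The 17,508 patients before clustering are taken as stated. They do not follow from an absolute 3-point difference under the stated error rates (at most 11,672 in total), but that is a separate matter. The power figures below are therefore conditional on the plan's own chain.

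- Primary outcome: design effect 1 + (48 − 1) × 0.08 = 4.76; 17,508 × 4.76 = 83,338 patients; 83,338 / 48 = 1736, or 868 per arm.
- Secondary outcome: 1 + (28 − 1) × 0.08 = 3.16; 17,508 × 3.16 = 55,325; 55,325 / 28 = 1976, or 988 per arm.
- Final target: 988 + 69 (7%) = 1057 per arm, 2114 in total.

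The chain reproduces. For the primary outcome the divisor is explicitly patients per practice, while the result is called GPs. This is correct only if one GP equals one practice.

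**2. How often a practice is split.** With independent 1:1 allocation (equal groups are planned; the ratio for the whole pool is not stated), a practice with k randomised GPs falls into both arms with probability 1 − 2 × 0.5^k:

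- k = 2: 0.50
- k = 3: 0.75

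**3. Dilution.** Let f be the share of GPs in two-GP practices and u the share of invited GPs who enrol. A control GP is exposed only if the partner was allocated to intervention (probability 0.5) and enrolled. With full spillover, and the enrolled GPs taken as fully exposed, the contrast shrinks by d = f × 0.5 × u. The documents give neither f nor u; f = 30–50% and the values of u are assumptions.

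**4. Power.** Power = Φ(3.2415 × √(2114/R) × (1 − d) − 1.96), where 3.2415 = 1.96 + 1.2816 and R is the number of GPs required for 90% power (1736 primary, 1976 secondary). The root is 1.1035 for the primary and 1.0343 for the secondary outcome. Without dilution, power is Φ(1.617) = 94.7% and Φ(1.393) = 91.8%.

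| Uptake u | d | Share of planned effect left | Power, primary | Power, secondary |
|---|---|---|---|---|
| 100% | 15–25% | 85–75% | 86–77% | 81–71% |
| 50% | 7.5–12.5% | 92.5–87.5% | 91–88% | 87–83% |
| 20% | 3–5% | 97–95% | 93–92% | 90–89% |

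Example, primary outcome, d = 15%: 3.2415 × 1.1035 × 0.85 − 1.96 = 1.08, Φ = 86%.

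**5. Reserve.** Power stays at 90% up to d = 1 − √(1736/2114) = 9.4% for the primary outcome, but only up to d = 1 − √(1976/2114) = 3.3% for the secondary outcome, which set the sample size.

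The table covers dilution only. The loss from several GPs of one practice in the same arm comes on top and cannot be quantified without the distribution of practice sizes.

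**The case against.** **Partial enrolment.** All eligible GPs in three regions are randomised, and only afterwards are those in the intervention group offered participation. Many control GPs in split practices will therefore have a partner who never enrols. This stands, and it is why the result is given by uptake.

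**Reserve in the sample size.** A reader might infer that power falls from 90% to about 79–68%. That needs 868 GPs per arm and full uptake. The planned number is 1057 per arm, where primary-outcome power starts at about 94.7%. At 20% uptake it stays above 90%.

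**Spillover may be partial.** The billing marker is set per GP, and for the other vaccinations the article compares participating with non-participating GPs. If rates were attributed to the individual GP, a split practice would keep some contrast, because communication training stays partly with the trained GP. A reader might infer that split practices carry no information at all. That holds only if the practice-level rate is used as defined. The definition of the primary outcome does say practice, so this objection reduces the size but does not remove the problem.

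**GP and practice may be used loosely.** The abstract speaks of the practices of 1057 GPs, and the patient survey draws 50 practices from 1057 GPs. This is compatible with one enrolled GP per practice, so a definite statement that the number of clusters is overstated is not proven. However, the article does not state such a rule, and one enrolled GP per intervention practice would still not prevent a practice partner from being in the control group.

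**Detail for the full protocol.** The level at which clustering is modelled can be left there. The unit of randomisation and the unit of the outcome cannot, because this article fixes both, and differently.

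**Conclusion.** The point holds. As written, the plan allows one practice to contribute to both arms, which biases the contrast towards zero, and it treats GP and practice as the same unit in the sample size although joint practices are included.

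The size is uncertain. It rests on assumptions about the share and size of joint practices, uptake among invited GPs and the degree of spillover. Across the range examined, primary-outcome power at 1057 GPs per arm lies between about 93% and 77%, so it may remain acceptable if uptake is low. The secondary outcome is more exposed, with about 81–71% at full uptake. This should be corrected, but the documents do not show that it defeats the trial.

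**What to change.** Use the practice as the single unit: assign all GPs of a practice to one arm, or declare one GP per practice eligible and keep the practice's other GPs out of the opposite arm. Define the outcome, the cluster count and the random effect at the same unit, and restate the recruitment targets in practices.

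If allocation is already done:

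- Identify practices split by randomisation from the randomisation list and the practice membership records of the regional physicians' associations. The article mentions only a pseudonymised GP marker in the billing extract, so whether practice membership can be linked has to be confirmed.
- Fit the practice as the cluster.
- Report the primary contrast with and without split practices. Split status is determined by the allocation itself, before any enrolment, so excluding these practices does not select on uptake or outcome.

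The cost is a change of wording, a linkage by practice, and fewer clusters for the same number of GPs. Where split practices are excluded, joint practices are under-represented, which is why both results should be shown.

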#### Secondary data

After submitting the certificate and vaccinating at least 20 patients aged 60 and older insured by a substitute health insurance fund in the first quarter of evaluation, the GP will receive an initial starter lump sum payment. Through this lump sum payment, the GP is marked as a participant in the billing data of the ASHIP and is available in a pseudonymised form for the summative evaluation over all quarters considered. Since secondary data (extract of pseudonymised contractual GP billing data according to § 295 SGB V) is used, the relevant data is available for both the intervention and the control group.

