The focus of the summative evaluation will be on a pre-post comparison between the intervention and control group, considering differences between the two groups that already existed before the intervention. For the post analysis, GP claims data from 7 quarters after the start of the intervention are available for analysis (07/01/2022–03/31/2024). Due to the still unknown impact of the COVID-19 pandemic on the next influenza vaccination season, a period of at least 24 months prior to the start of the intervention will be considered for pre-analysis – meaning the vaccination and immunisation uptake rates achieved prior to the intervention. Because influenza vaccination should occur annually, comprehensive information on the baseline population and the number of vaccinated persons is available. The determination of vaccination uptake rates, on the other hand, is more challenging because the size of the population is unclear due to the long periods of time between booster vaccinations. Persons aged 60 and older are recommended to receive a booster vaccination against tetanus, diphtheria, and pertussis only every 10 years. A booster vaccination against pneumococci after 6 years (or later) is beneficial but not generally recommended by the STIKO. Furthermore, there is no recommendation for a booster vaccination against herpes zoster after the basic immunisation has been completed. The available data does not allow to identify if patients aged 60 and older got a booster vaccination against tetanus, diphtheria, and pertussis in the past 10 years and if patients aged older than 60 have already been vaccinated against pneumococci or herpes zoster. Therefore, we will analyse the increase in the vaccination uptake rate among participating GPs compared to non-participating GPs. Provided that the necessary number of cases is achieved, subgroup analyses for individual vaccinations (e.g., pneumococci) are planned.

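### Intervention GPs are marked for the outcome evaluation through a post-randomisation count of 20 vaccinated patients, with no matching condition stated for controls

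*Protocol article*

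**What the plan says.** All references are to the Protocol article.

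- **Eligibility and allocation (Recruitment).** The pool is GPs "who have vaccinated patients aged 60 and older insured by the substitute health insurance fund in the past". No minimum count is set. These GPs are randomised within ASHIP region. Those allocated to the intervention are then offered participation and complete the online training.
- **Marking (Recruitment, Secondary data).** The starter lump sum is due after the certificate and after "vaccinating at least 20 patients aged 60 and older insured by a substitute health insurance fund in the first quarter of evaluation". The text goes on: "Through this lump sum payment, the GP is marked as a participant in the billing data of the ASHIP", and the GP so marked "is available in a pseudonymised form for the summative evaluation over all quarters considered".
- **Controls (same section).** The text says only that "the relevant data is available for both the intervention and the control group". No volume condition is given for them.
- **Primary outcome (Measures, Secondary data collection).** "The rate will be computed as the fraction of the amount of vaccinated patients insured by a substitute health insurance fund aged 60 and older", divided by all such patients of the practice, measured annually.
- **Comparison (Summative evaluation: secondary data).** The focus is a pre-post comparison between the groups that takes account of differences present before the intervention. For the vaccinations other than influenza, "we will analyse the increase in the vaccination uptake rate among participating GPs compared to non-participating GPs". The post period is the 7 quarters from 1 July 2022 to 31 March 2024.

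**The concern.** The stated route into the analysed intervention group runs through a count of vaccinated patients that is observed after randomisation and inside the evaluation period. It concerns the same patient group as the outcome numerators. A practice that vaccinates few patients in the qualifying quarter, including one where the intervention did not work, does not acquire the mark, while its counterpart in the control group faces no such hurdle. Randomisation then no longer protects the comparison, and a positive difference can appear when the intervention does nothing. The Discussion says the results inform a decision on inclusion in standard care, so a one-sided error towards success matters.

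**Working it through.** **1. The plan's own figures (Sample), taking its 17,508 as given.** Design effect = 1 + (m − 1) × ICC.
- Influenza: 1 + 47 × 0.08 = 4.76; 17,508 × 4.76 = 83,338; ÷ 48 = 1736 GPs, 868 per group.
- Other vaccinations: 1 + 27 × 0.08 = 3.16; 17,508 × 3.16 = 55,325; ÷ 28 = 1976 GPs, 988 per group. 988 + 69 = 1057.

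These steps reproduce.

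**2. Inputs for the null check.**
- From the article: 48 vaccinated per practice and ICC 0.08 (Sample); rate 47.3%, the national figure for ages 60 and older in 2020/2021 (Background); target 3%, read as points (Sample).
- Derived: eligible patients per practice = 48 / 0.473 ≈ 101.
- Assumed, not in the documents: coefficient of variation of practice size 0.5; correlation r of practice rates between years 0.6 to 0.95; share f of the season's vaccinations in the qualifying quarter 50% to 100%; one season before and one after; the count is influenza vaccinations.

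**3. Model.** With no effect, Y₁ ~ Bin(N, p₁) and Q ~ Bin(Y₁, f); a GP is marked if Q ≥ 20. The rule acts on the intervention side only.
- Post-only bias B = E[Y₁/N | Q ≥ 20] − E[Y₁/N].
- Difference-in-differences bias = E[Y₁/N − Y₀/N | Q ≥ 20], which is zero only if the marking carries no information about same-season activity beyond the stable practice level.

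**4. Results at r = 0.8, each practice weighted equally.**

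| f | GPs marked | Post-only | Difference-in-differences |
|---|---|---|---|
| 0.5 | 54% | +5.9 | +1.7 |
| 0.7 | 73% | +3.8 | +1.2 |
| 1.0 | 86% | +2.2 | +0.7 |

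Weighted by patients at r = 0.8, the difference-in-differences bias is +0.4 to +1.2. Over the whole grid it runs from +0.2 (r = 0.95, f = 1, patient-weighted) to +2.8 (r = 0.6, f = 0.5, practice-weighted). It was positive in every scenario.

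**5. Hand check.** The pre-period removes roughly a fraction of B equal to the correlation between observed yearly rates.
- True between-practice variance: 0.08 × 0.473 × 0.527 = 0.0199.
- Sampling variance, gamma sizes: 0.92 × 0.473 × 0.527 × (1/101) × (4/3) ≈ 0.0030.
- Observed correlation at r = 0.8: 0.8 × 0.0199 / 0.0229 ≈ 0.695, so about 0.305 of B remains.
- 0.305 × 5.9 = 1.8; × 3.8 = 1.2; × 2.2 = 0.7. This agrees with the table.

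**6. False positives at r = 0.8.** Variance of a practice's change ≈ 2 × 0.0229 × 0.305 = 0.0140. With 1057 GPs per group, SE = √(2 × 0.0140 / 1057) ≈ 0.51 points. Biases of 0.7, 1.2 and 1.7 then give two-sided rejection in about 28%, 65% and 92% of null trials, instead of 5%.

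**7. If the count is not influenza.** With a qualifying count that depends only on practice size and a stable practice propensity (assumed mean 28, coefficient of variation 0.5, r = 0.8), the post-only bias in the influenza rate was +3.7 points, but the difference-in-differences bias was about zero (−0.03). The count then feeds the numerator of the secondary outcome. The article says the denominator of that outcome is unclear, so no size can be given for it.

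**The case against.** The article says how a GP is marked. It does not say in so many words that intervention GPs below 20 are discarded, nor that controls enter unfiltered. A fuller plan, not shown here, could define the groups by randomisation or apply one volume rule to both arms. This limits how firmly the consequence can be asserted, but it does not turn the point into missing detail: the article does state a mechanism, and that mechanism is one-sided.

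Three further objections stand in part.
- **Vaccine and quarter are not named.** The post period starts on 1 July 2022, so the qualifying quarter may be July to September. A reader might infer that the primary outcome is certainly biased, or that no difference-in-differences analysis could remove the bias. Neither follows: step 7 shows a case where the influenza contrast is essentially untouched.
- **The planned contrast is pre-post, with clustering and influencing factors considered.** The post-only figures therefore overstate what the planned analysis would show. In this kind of model the bias also sits in the qualifying season, and the following season showed about none. Averaging two such seasons would halve the range to about +0.1 to +1.4.
- **Participating against non-participating.** A reader might infer that unmarked intervention GPs are moved into the comparator for the primary outcome. That sentence follows the discussion of boosters with unclear denominators, so in context it concerns the other vaccinations.

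A single false-positive rate should not be quoted either. For r of 0.8 to 0.95 it ranges from about 25% to 95%, depending on assumptions the article does not supply.

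**Conclusion.** The point holds in this form. As written, the intervention group is formed using post-randomisation vaccination activity, on one side only, and this favours the intervention. Pre-post analysis reduces the bias but removes it fully only if the qualifying count shares no same-season variation with the outcome. If the count is mainly influenza vaccinations, the spurious difference-in-differences is about +0.2 to +2.8 points under the assumptions listed, against a target of 3. If it is mainly other vaccinations, or the quarter precedes most influenza vaccination, the direct bias moves to the secondary outcome and the influenza contrast may be little affected. Direction is well supported by the text; size is not derivable from it. Voluntary acceptance of the offer and the certificate requirement are further selection on the intervention side, not included in these figures.

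**What to change.** - Keep the 20-patient rule as a condition for payment only, and do not use the payment code to define the analysis group.
- Carry the randomised arm in the pseudonymised billing extract and make the as-randomised comparison the main one.
- Add an analysis of certificate-holders, labelled as non-randomised.
- If a minimum volume is wanted, define it on a pre-intervention period and apply it identically in both arms. The choice of period should fit the plan's own separation of pre-pandemic and pandemic baselines.

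**Cost.** An arm flag in the extract and revised wording. The ASHIPs run recruitment, receive the certificates and hold the billing data, so no new collection appears necessary. Whether they may flag GPs who declined the offer is not settled in the article and has to be checked.

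**Downside.** Low-activity GPs and, in the as-randomised analysis, GPs who declined enter the intervention arm, so the estimate is diluted. If a proportion u takes part, a 3-point effect becomes 3 × u; with u = 0.5 (an assumption, since uptake is not given) it is 1.5 points. The stated power for a 3% effect should be read as applying to participating GPs. Power for the as-randomised analysis also depends on how many randomised GPs it includes, which the article does not state.
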